#### Intermediate analysis

The hypothesis of a 30% difference between the two groups is conservative compared to the 50% reduction reported by Hakim [39]; a difference of only 30% between the two groups should already be clinically relevant. An interim analysis is therefore planned after the enrolment of 44 patients. The overall alpha risk will be adjusted according to the Bonferroni method and will be 2.5% (5% / 2). A *p* value < 0.025 will therefore be considered statistically significant. If this initial analysis is statistically significant (*p* < 0.025), the independent monitoring committee may decide to stop the study without waiting for the planned recruitment. Otherwise, the study will be continued until the inclusion of 88 patients.

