### Population

#### Number of patients needed

The sample size calculation is based on a previous study that investigated tetracosactide in PDPH [39] and, retrospectively, on observational data obtained from our hospital database. The primary endpoint is the rate of blood patch in the two groups. We defined the efficacy of tetracosactide as a decrease in blood patch use by 30% in the tetracosactide group, a clinically relevant difference reducing the need for invasive treatment and replacing it with an easily administered treatment that has a known safety profile.

In our centre, 90% of patients with PDPH after epidural analgesia receive a blood patch. The study reported by Hakim [39] found a greater than 50% decrease in PDPH incidence and blood patch use after prophylactic treatment with tetracosactide, in a context of epidural analgesia. We therefore need to include 44 subjects in each group, given a power of 0.80 and type I error of 0.025 (α = 2.5% Fisher’s exact test, power of 80%, p1 = 0.9; p2 = 0.6), to reduce the blood patch requirement by 30%. Thus a total of 88 patients need to be randomised.

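### The plan calls 2.5% the overall alpha, but 2.5% is the level of each of two looks in a 5% design; the Bonferroni split also gives up about 2 points of power that a Pocock boundary would return at no cost

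*Protocol article*

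**What the plan says.** The Intermediate analysis section of the protocol article sets the first look: "An interim analysis is therefore planned after the enrolment of 44 patients". It then fixes the error rate: "The overall alpha risk will be adjusted according to the Bonferroni method and will be 2.5% (5% / 2"), and gives the decision threshold as a p "value < 0.025 will therefore be considered statistically significant". If the interim result is not significant, a second look follows: "Otherwise, the study will be continued until the inclusion of 88 patients".

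The section on the number of patients needed uses the same level, "given a power of 0.80 and type I error of 0.025", with the test named in the bracket ("α = 2.5% Fisher’s exact test, power of 80"%) and planning rates of 0.9 and 0.6. The result is "We therefore need to include 44 subjects in each group", 88 in all.

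Taken together, the plan has two looks, each at p < 0.025. Neither section says whether the level is one-sided or two-sided.

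**The concern.** The label and the rule do not agree. If 2.5% were the overall risk, two looks could not each be run at 2.5% under Bonferroni; each would have to be run at 1.25%. If each look is run at 2.5%, as the threshold and the sample size both imply, the overall level is 5%. Someone who takes the sentence at its word will report the wrong designed error rate.

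The second part concerns efficiency. The 44 interim patients are half of the final 88, so the two test statistics are strongly correlated. Bonferroni ignores this and leaves part of the 5% unused. Unused alpha matters more where patients are hard to find. The Trial status section reports 25 enrolled between October 2016 and May 2019, and the Discussion concedes that the sample size could be too small if the control rate is below 90%.

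**Working it through.** **Inputs.** From the sample-size section: rates 0.90 and 0.60, Fisher's exact test, level 0.025, 44 per arm. From the Intermediate analysis section: looks at 44 and 88 patients, p < 0.025, continue to 88 if not significant. Assumed: equal allocation, so 22 then 44 per arm, and a two-sided test. The two-sided assumption rests on the sample size: one-sided 0.025 would need only 36 per arm.

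**1. The plan's own figure.** Exact power of the two-sided Fisher test is the sum of Bin(x; n, 0.9) × Bin(y; n, 0.6) over all tables with p < 0.025. It first reaches 80% at n = 43 (81.1%) and is also 81.1% at n = 44. The normal-approximation formula gives 45 with continuity correction and 39 without. The stated 44 is reproduced.

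**2. The overall error of two looks at 0.025.**
- Bonferroni bound: 2 × 0.025 = 0.05.
- Normal theory: the information fraction is 44/88 = 0.5, so the correlation between the two statistics is √0.5 = 0.707. The critical value is 2.241 at both looks. Then 1 − P(|Z₁| < 2.241 and |Z₂| < 2.241) = 0.0428.
- Exact two-stage Fisher calculation, largest value over common event rates: 0.0224.

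No version exceeds 5%. The 2.2% comes from the discreteness of Fisher's test.

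**3. Comparison of boundaries at 0.90 versus 0.60.** All outcomes at 22 and then 44 per arm were enumerated, with Fisher p-values at each look. The boundaries were solved for an overall two-sided 5% with correlation √0.5. Expected N = 88 − 44 × P(stop at interim), taking a significant interim as a stop.

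| Rule (interim / final p) | Stop at 44 | Overall power | Max. exact type I error | Expected N |
|---|---|---|---|---|
| Planned Bonferroni, 0.025 / 0.025 | 42.2% | 82.3% | 2.2% | 88 − 44 × 0.4224 = 69.4 |
| Pocock, 0.0294 / 0.0294 | 43.0% | 84.5% | 2.7% | 88 − 44 × 0.4296 = 69.1 |
| O'Brien-Fleming, 0.0052 / 0.0480 | 20.8% | 87.9% | 2.9% | 88 − 44 × 0.2082 = 78.8 |
| Lan-DeMets O'Brien-Fleming, 0.0031 / 0.0490 | 14.8% | 87.9% | 3.1% | 88 − 44 × 0.1479 = 81.5 |

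Pocock gains 84.5 − 82.3 = 2.2 points and is no worse on early stopping or expected size. The O'Brien-Fleming types gain 5.6 to 5.7 points, at a cost of about 9 to 12 more patients on average (78.8 − 69.4 = 9.4; 81.5 − 69.4 = 12.1). With normal approximations their gain is about 4 to 5 points.

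**The case against.** The strongest defence is that the section prints its own arithmetic. With 5% / 2, the Bonferroni name and the 0.025 threshold all in view, a careful reader can see which figure is the total and which is the level per test. "Overall" is then a loose word, and the decision rule is unaffected. Bonferroni over two looks is valid, and the trial was sized for it. All of this stands, and it limits the point to a label and a small loss.

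Three stronger readings are tempting, and the documents do not support them.

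- A reader might infer that the type I error is inflated, because two looks at 2.5% exceed a stated 2.5%. The intended total is 5% and the rule stays under it. With the planned Fisher test the overall error is even below 2.5%, but that follows from the test's conservatism and does not make 2.5% the designed overall level.
- A reader might infer that the trial is underpowered. On its own assumptions it has 81.1% at the final test alone and 82.3% overall.
- A reader might infer that O'Brien-Fleming is simply better, or would allow a much smaller trial. With those levels, 36 per arm (72 in all) does give 80.1% power, but setting 72 against 88 compares maximum sizes only. Expected N would be 67.9 against 69.4, a saving of 1.5 patients with slightly lower power.

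O'Brien-Fleming also works against the stated reason for the interim. The section motivates the look by the larger reduction, about 50%, in the earlier prophylaxis trial. If blood patch use did halve (0.90 versus 0.45), the planned rule would stop at 44 with probability 80% (expected N 53) and the Lan-DeMets boundary with probability 52% (expected N 65). Power would exceed 99% under both.

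**Conclusion.** The point holds as a mislabelled error rate and a small avoidable inefficiency. The Intermediate analysis section should call 2.5% the level per look of a design with 5% overall two-sided alpha. The rule is valid, conservative and meets its power target. The loss that can be recovered at no cost is 2.2 points of power, by moving from Bonferroni to Pocock. The gain to about 88% under an O'Brien-Fleming-type boundary is real, but it is paid for in early stopping and expected size, and choosing it is a matter of preference.

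These figures assume a two-sided test, equal arms at both looks, rates of 0.90 and 0.60, and a stop whenever the interim is significant. The last is not settled in the article: the Intermediate analysis section leaves stopping to the monitoring committee's discretion, while the Trial status section says the study will be discontinued. Power and type I error do not depend on it if a significant interim counts as a rejection; expected N does.

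**What to change.** In the Intermediate analysis section, state that the overall two-sided alpha is 5% and give the level of each look separately. In the sample-size section, state the overall 5%, the level used at the final look, and that the test is two-sided.

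Before the interim is run, replace 0.025 / 0.025 with a boundary that uses the correlation between looks. Pocock with p < 0.0294 at both looks is the direct substitute: the same 88 patients, an interim stop of 43% against 42%, power of 84.5% against 82.3%, and exact type I error of at most about 2.7%. The cost is an amendment of the wording, with no extra patients.

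If the sponsor puts final power above early stopping, an O'Brien-Fleming-type boundary (about 0.003 to 0.005 at the interim and 0.048 to 0.049 at the end) is an option. The amendment should then state what is given up: the chance of stopping at 44 falls from 42% to between 15% and 21%, and expected sample size rises from about 69 to between about 79 and 81. Either change must be fixed before any unblinded interim result is seen. If the interim has already been run, correct the label only and keep 0.025 for the final test.

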### Ethical approval

This trial is conducted in accordance with the protocol and in compliance with the moral, ethical and scientific principles governing clinical research as set out in the Declaration of Helsinki (1989) and Good Clinical Practice (GCP). It is also conducted in accordance with French legislation (Public Health Code; Act No. 2004–806 of 9 August 2004). It is registered in the Clinical Trial Protocol Registration and Results System: NCT02813655 (registration date: 24 June 2016). An ethics committee (*Comité de Protection des Personnes sud Est V*, CPP) has approved the study for both participating sites on 6 April 2016. The national drugs authority (*Agence Nationale de Sécurité du Médicament et des Produits de Santé*, ANSM) authorised this trial (authorisation date: 18 April 2016).

### Adverse events management

During the study period, adverse events will be reported and recorded in the participants’ CRF. Adverse events include any new abnormality observed upon clinical examination, occurring during the study treatment injection or the follow-up period, or any allergic reaction to the treatment. The severity of adverse events will be graded as mild, moderate, severe, life threatening, or death, and the potential relationship between the adverse event and the study treatment will be assessed by clinical judgment. If an adverse event requiring hospitalisation extension or causing a medically critical situation occurs, the event will be recorded as a severe adverse event. All severe and life threatening adverse events or death will be reported to the investigator and to the sponsor within 24 h after the information has been collected. The sponsor will report all such events to legal authorities (ANSM and CPP). The investigator must follow patients until the adverse event has been resolved. All adverse events collected will be described in the trial publication. A severe adverse event is the only reason for unblinding participants and providers before the end of the study. It will be performed by the poison control centre (Anti-poison Centre) which is independent of the study and is the only party with access to the randomisation list.

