### Intervention protocols

During the post-partum period, patients are usually followed by midwives. In case of headache, whether an accidental dural puncture is diagnosed or not, the anaesthesiologist is informed by the midwives. Therefore, any symptomatic patient is examined by an anaesthesiologist. The study investigators are the anaesthesiologists working in the maternity department of the two centres.

Patients are enrolled when diagnosed with PDPH based on the anaesthesiologist’s clinical evaluation. They are randomised to receive intravenous tetracosactide or placebo. In the study group, patients receive a single intravenous injection of 1 mg tetracosactide (Synacthen®, Sigma-Tau laboratory, Roma, Italy). Four vials containing 0.25 mg tetracosactide (in 1 ml of solvent) are reconstituted in 100 ml of normal saline (0.9% NaCl). This solution is infused intravenously over 20 min. In the control group, patients receive an equal volume of normal saline: 104 ml over 20 min. The whole intervention is administered over a 20-min course and therefore is not modifiable once begun except for the occurrence of a side effect. A side effect is defined herein as any new abnormality observed upon clinical examination, occurring during the injection. In this case, the treatment is immediately stopped but monitoring and data collection continues.

Standard analgesic medication, as concomitant treatments, is also initiated in both groups from the beginning of headache, as follows:
for mild headache (NRS < 3/10): 1 g paracetamol and 400 mg ibuprofen orally every 6 hfor moderate headache (NRS = 3): nefopam 20 mg and/or a combination of paracetamol 300 mg and opium 10 mg is given in addition every 4 hfor severe headache (NRS ≥ 4): morphine 10 mg orally every 4 h can be added as required

These treatments are adjusted daily.

The primary and secondary endpoint, including tolerance criteria, are evaluated blinded during infusion of the study treatment, 2–6 h later, 1 day, 2 days, 3 days and between 13 and 17 days post-treatment by the investigator. The latter is conducted by phone call in order to increase the complete follow-up. The total duration of the study is therefore 13 to 17 days. Any alternative analgesic intervention required after receiving the study treatment is reported at each time point as indicated above. The study timeline is summarised in Fig. 2.

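### New hospital admission is missing from the triggers that make an adverse event reportable, so a non-critical readmission graded mild or moderate escapes the 24 h and authority reports

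*Protocol article*

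**What the plan says.** All the relevant rules stand in the Protocol article, mostly under Adverse events management.

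- Collection: adverse events count when "occurring during the study treatment injection or the follow-up period". Trial design likewise says that they are collected throughout the study.
- Intensity: "The severity of adverse events will be graded as mild, moderate, severe, life threatening, or death".
- Escalation: "If an adverse event requiring hospitalisation extension or causing a medically critical situation occurs, the event will be recorded as a severe adverse event".
- Expedited reporting: "All severe and life threatening adverse events or death will be reported to the investigator and to the sponsor within 24 h", counted from when the information is collected. The sponsor then passes these events to the national drugs authority and the ethics committee.
- Early unblinding: "A severe adverse event is the only reason for unblinding participants and providers before the end of the study".

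Intervention protocols fixes the length of follow-up: "The total duration of the study is therefore 13 to 17 days". Of the last contact it says: "The latter is conducted by phone call in order to increase the complete follow-up". Secondary endpoints makes length of hospital stay an outcome, counted in days from inclusion to day 15.

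**The concern.** The escalation sentence makes the need for hospital care a sufficient reason to escalate an event, whatever its intensity grade. It expresses that need only as the lengthening of a current stay. Once a woman has gone home there is no stay to lengthen, and needing to come back in is not listed. The rule therefore sorts events partly by where the woman was when they began, which says nothing about how much they matter.

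Two safety reports depend on this label: the one to the sponsor within 24 h and the sponsor's onward report to the authorities. Safety is part of the stated aim of the study. An event that puts a recently delivered woman back in hospital after an investigational infusion is one that the sponsor would want to hear about promptly.

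**Working it through.** The article states no figure on this point and no arithmetic decides it. The check is to read the rules together and see which events reach the 24 h and authority reports.

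**Routes into the reports.** There are three:

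1. The event is graded severe or life threatening, or is fatal.
2. The event causes a medically critical situation.
3. The event requires the hospital stay to be extended.

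**Applying them before and after discharge.**

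| Event | Woman still in hospital | Woman discharged, then admitted |
|---|---|---|
| Graded severe or life threatening, or fatal | Reported (route 1) | Reported (route 1) |
| Graded mild or moderate, medically critical | Reported (route 2) | Reported (route 2) |
| Graded mild or moderate, not critical, needs hospital care | Reported (route 3: stay extended) | **Not reported** (no route applies) |

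Only the third row changes with discharge. In that row the intensity and the need for hospital care are the same in both columns.

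**Can the third row occur within the trial?** Follow-up lasts 13 to 17 days and events are collected throughout. Length of stay is an outcome measured up to day 15, and the final contact is by telephone; both suggest that discharge normally falls within follow-up. The situation is therefore foreseeable, although the article gives neither a discharge day nor a readmission rate.

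**When would the study hear of it?** The scheduled contacts after treatment are at 2 to 6 h, on days 1, 2 and 3, and at days 13 to 17. Between day 3 and the closing call there is a gap of 13 − 3 = 10 to 17 − 3 = 14 days with no scheduled contact. The 24 h clock starts only when the information is collected. For some admissions the closing call may therefore be the first scheduled chance to learn of them, and the article does not say that the call asks about admissions.

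**Why the labels need separating.** The word severe serves both as an intensity grade and as the category that carries the reporting duty, and the unblinding rule uses it too. Simply adding admission to the list of things recorded as severe would also open early unblinding to mild or moderate, non-critical admissions. Under Intervention protocols (the text following Fig. 2), the decision to perform a blood patch, which is the primary endpoint, rests on the anaesthesiologist's clinical judgement. Extra unblinding could therefore reach the people who make that decision.

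**The case against.** **The rule is wider than extension of stay.** A reader might infer that only extension escalates an event, or that no readmission triggers a report. The text does not support that. The same sentence adds medically critical situations, and the grading route brings in severe and life-threatening events and deaths regardless of location. Many readmissions would qualify by one of these routes. This objection stands and limits the point to the third row of the table.

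**The article condenses a fuller protocol.** Ethical approval states conduct under Good Clinical Practice and French law, and the full protocol may hold a complete list of criteria. This lowers confidence that the gap exists in practice. It does not dispose of the point, because the article prints an operative rule with named triggers, and that rule is incomplete as printed. If the full protocol names admission, the article needs only to be aligned with it.

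**The event is not lost.** All adverse events are recorded, followed until resolved and described in the publication, and the length-of-stay outcome should pick up days spent back in hospital by day 15. This is correct. What is missing is the prompt report; the data would still exist.

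**The size is unknown.** It is tempting to say that the gap covers most of follow-up. With 15 days of follow-up, an assumed discharge on day 3 leaves (15 − 3)/15 = 80% of days after discharge, day 5 leaves (15 − 5)/15 = 67%, and day 8 leaves (15 − 8)/15 = 47%. The answer depends entirely on the assumed day. Nor is a share of days a share of events, since the treatment is a single 20-minute infusion. This objection stands.

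**Bias in favour of the drug is speculation.** One might argue that a drug that shortens stay leaves treated women less time in which extension can apply. That needs a shorter stay under treatment and enough mild or moderate, non-critical readmissions to matter among 88 women. The article shows neither, and it specifies no separate comparison of severe events. The tolerance endpoint covers all events.

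**Conclusion.** The point holds in a narrow form. As printed, an admission after discharge for an event graded mild or moderate and not judged medically critical is reported neither to the sponsor within 24 h nor to the authorities, whereas the same event before discharge would be. This follows from the wording alone. It rests on two readings: that extension of a hospital stay does not include a new admission, and that the article prints the rule actually in force.

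No numerical magnitude and no direction of bias is claimed. The primary analysis is unaffected. The consequence is one of safety oversight, and it is worth correcting because the remedy is small and, at the time of the article, the trial was still recruiting, with 25 of 88 women enrolled. That such an admission does not open early unblinding is not counted here as a defect.

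**What to change.** Under Adverse events management, change the trigger to: *an adverse event requiring hospital admission or extension of the hospital stay, or causing a medically critical situation*. Apply it to the 24 h report and to the report to the authorities.

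Record this reporting category in its own field, separate from the five-level intensity grade. Word the unblinding sentence so that it stays limited to the events that permit unblinding now. An admission that is neither critical nor graded severe or worse would then be reported without opening the allocation.

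Add a question on hospital admissions since the last contact to the existing call at days 13 to 17. If the full protocol already names admission, correct the article to match.

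The cost is one phrase, one field on the case report form, one question at a call that already takes place, and probably a few more expedited reports.

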### Protocol amendment

Because patient enrolment/inclusion was more difficult than expected, the protocol was amended (January 2017) to extend inclusion from PDPH due to a dural puncture carried out by large Tuohy needle to all postpartum PDPH, i.e. PDPH related to a large dural puncture and PDPH related to small needle (25-27G) for spinal anaesthesia. For this reason, a second amendment (November 2018) extended the inclusion period until October 10, 2021.

## Discussion

We propose herein a protocol to investigate the use of tetracosactide, an ACTH analogue, to treat PDPH. Blood-patch is currently the gold standard for PDPH treatment, and tetracosactide could be interesting as it would reduce the need for the invasive procedure and replace it with an easily administered treatment that has a known safety profile. Given previous results obtained in small groups of patients, evidence for the efficacy of ACTH analogues for PDPH treatment remains limited.

Initially, the inclusion was limited to PDPH due to a dural puncture carried out by a large Tuohy needle. Because patient enrolment/inclusion was more difficult than expected, the protocol was amended to extend inclusion to all postpartum PDPH. This widening of the inclusion criteria raises the issue of population heterogeneity, which we hope to limit by the randomisation process.

Since the management strategy of PDPH (using blood-patch and non-invasive treatments) is not clearly defined, the rate of blood-patch varies. Rucklidge, for example, described that 50 blood-patches were received by 144 patients treated for PDPH after epidural anaesthesia over 20 years in the hospital in which he practiced [47]; the blood-patch rate was therefore 35%. In the study reported by Aya et al. all patients (100%) treated for PDPH after epidural obstetric anaesthesia in their unit received a blood patch [48]. Therefore, a potential limitation of the study described herein is that the sample size could be insufficient if the rate of blood patch in the control group is lower than 90%.

